### 2.3. Intervention Protocol

#### 2.3.1. Tai Chi Group

Participants in the intervention group will attend a 60-min Tai Chi practice session twice a week for three months. This duration is supported by previous studies that even a short duration of 12-week intervention of Tai Chi can improve physical performance of healthy elderly people [25] and patients with chronic illnesses [10]. We choose three months for our subjects as the training period to balance the time for optimal result and the issue of compliance. Based on experience in a chronic illness rehabilitation program, intensive intervention beyond 12 weeks would cause participants to drop out of the study. High attrition rate would seriously affect the validity of the study. Moreover, normally the Tai Chi instructor will teach a new form in each session after revising the taught forms. It needs 24 sessions to complete the 24 forms, which accounts for three months.

The Tai Chi program is a 24-form Yang style Tai Chi, which was modified and tailor-made for our target population by two Tai Chi experts. This modified 24-form Tai Chi is designed for easy learning and mastery in a shorter period. The modified forms were also reviewed by an experienced physiotherapist to confirm their safety and feasibility to be used on the target participants. During the Tai Chi practice sessions, an experienced Tai Chi instructor will lead the participants who will replicate the motions, postures, and speed of movement. Participants will be encouraged to perform self-practice at home for 30 min per day, for at least 5 days per week. A self-recorded logbook will be used to monitor participants' adherence. Participants will be required to record their frequency and duration of self-practice in a logbook on a daily basis. The logbook will be checked by the research assistant weekly at the Tai Chi class. A compliance rate of ≥80% is considered as adherence.

#### 2.3.2. Walking Group

As recommended by the Centre for Health Protection, aerobic exercise should be done at least at moderate intensity, such as brisk walking, for at least five days per week [26]. Moderate intensity activity could be expressed as 50% to 70% of maximum heart rate. Maximum heart rate is estimated by “220 minus age” [27]. Participants in the walking group will be recommended to perform brisk walking (5 to 6 km/h) for 30 min every day, for at least 5 days per week. They may practice continuously or intermittently in bouts of at least 10 min to accumulate 30 min [27]. Participants will be given a pulse watch to measure their heart rate during brisk walking. They will be advised to achieve an individualized heart rate equivalent to moderate intensity exercise according to their age. A diary will also be given to the participants to record their heart rate, frequency and duration of brisk walking. The research assistant will contact participants by phone weekly to monitor their adherence. A compliance rate of ≥80% is considered as adherence.

#### 2.3.3. Control Group

Participants in the control group will be advised to maintain their routine activities. No extra exercise will be recommended. During the study period, all subjects will continue their prescribed medical treatments, if any. To enhance the internal validity of the study findings, participants in the walking and control groups will be arranged to join non-health-related social activities regularly for three months. The purpose of maintaining regular gatherings for the participants is to balance the psychosocial effect of weekly gatherings of the Tai Chi group during the process of Tai Chi training.

### 2.4. Outcome Measurements

#### 2.4.1. Primary Outcomes

(a)BP: Two measurements of BP will be measured from the seated position after the participant has rested for 10 min. The average of the two values will be used for study purposes. SBP and DBP will be recorded. Only one digital blood pressure monitor will be used for all BP measurements for all participants. Coefficients of variation (CV) of SBP and DBP were reported <10% in a previous study [22]. CV is a unit-less measure that depicts the size of the SD relative to its mean.

#### 2.4.2. Secondary Outcomes

(a)After an 8- to 10-h fasting, blood samples will be taken by using a finger-stick for the following measurements using auto-analyzers:
(i)Fasting blood sugar (FBS)(ii)Glycated hemoglobin (HbA1c)(iii)Total cholesterol (TC), triglyceride (TG), high-density lipoprotein (HDL) and low-density lipoprotein (LDL). CVs of all these six variables were <0.31 in previous studies [22,28]
(b)BMI will be calculated as weight (kg) divided by the square of height (m). Height and weight (measured to the nearest 0.1 kg) will be measured with the subject wearing light clothing without shoes(c)Waist circumference will be measured to within 1 mm by using a plastic measuring tape at midway between the lowest rib and the iliac crest with the subject standing at the end of gentle expiration. CV of waist circumference was reported <0.13 in a previous study [29].(d)Frequency and duration of self-practice of Tai Chi/brisk walking from a self-recorded logbook(e)Perceived stress scale (PSS-10)

Ten self-report items measure the degree to which situations in one’s life are appraised as stressful and the current levels of experienced stress in the last month. Summative scores range from 0 to 40, with a higher score indicating higher stress level. These scores have been used as outcome measures of experienced levels of stress. The psychometric properties of the Chinese version of PSS-10 were satisfactory with Cronbach’s alphas >0.75 in a local study for Chinese cardiac patients [30]. CVs of PSS-10 were reported to be 0.44 at baseline, 0.50 at 6 weeks and 0.48 at 12 weeks in a previous study [31].

(f)Quality of life: Short-form 12 health survey (SF-12v2)

The SF-12v2 is a popular generic health-related quality of life measure. This 12-item questionnaire measures functional health and well-being from the perspective of clients. The survey has favorable internal consistency and test-retest reliabilities (from 0.67 to 0.82). SF-12v2 is valid, reliable, and sensitive for the Chinese population with CVs for both physical and mental component summary <0.2 [32].

### 2.5. Data Collection Procedure

To minimize researcher bias, research assistants (RA) who are responsible for data collection will be blinded to the group allocation of the subjects. They will receive a briefing session explaining procedures for data collection. The RAs will also be trained in using the finger-stick for collecting blood samples, and in the procedures of using the auto-analyzers. Inter-rater reliability of the data collection procedures among the RAs will be examined.

Informed consent will be obtained from the eligible subjects. Data will be collected through physical assessments and questionnaires. The medical records of all participants will be reviewed for demographic information, medical history, and comorbidities. Pre-test at baseline (T1) and post-test at three months (T2) measurements will be obtained. To monitor the long-term compliance behaviors of subjects on Tai Chi practice and walking exercise, follow-up evaluations will be conducted at six months (T3) and nine months (T4). Twenty participants per month are anticipated to participate in the main study. Therefore, to recruit 246 participants, 12 months will be required to recruit the required number of participants, and another 9 months are needed to complete all T4 data collection points. Figure 1 shows the flowchart of the study design in accordance with the CONSORT guidelines for randomized controlled trial (RCT) [33].

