For a home program, walking is usually adopted for exercise training. However, adherence to regular brisk walking is still inadequate [7]. Hence, current literature lacks evidence to support the sustaining beneficial effects of brisk walking on CVD risk reduction. Tai Chi is a safe exercise that requires an energy expenditure that is similar to brisk walking [20]. However, Tai Chi is not known to provide the same cardiovascular training effect as brisk walking. Comparing the health benefits between Tai Chi and brisk walking, particularly to people with CVD risk factors, have been rarely studied in healthcare research. To address the gaps of knowledge, this study aims to compare the effects of Tai Chi with brisk walking in reducing modifiable CVD risk factors. If Tai Chi is as good as or even better than regular brisk walking, this would be of considerable public health importance as it is socially acceptable and attractive and might well be better taken up and sustained than brisk walking.

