### 2.6. Data Analysis

(1)For demographic data, frequency and percentage will be used to summarize and present categorical variables, whereas mean and SD will be used for continuous variables. Normality of continuous variables will be examined using skewness and kurtosis statistics and normal probability plot. The baseline characteristics among the three groups will be compared using chi-square test and one-way analysis of variance (ANOVA).(2)Generalized estimating equations (GEE) models with appropriate link function and distribution assumption, will be used to compare the changes in outcome variables across time among the three groups with adjustment for those baseline characteristics showing statistically significant differences among the groups. In the GEE model for each outcome, two dummy variables will be set to correspond the three groups with the control as reference. Another three dummy variables will be set to represent the four time points (T1 to T4) with the baseline (T1) as the reference. The interaction-terms of group by time will also be included in the GEE models to assess the differential changes of the outcomes across time and between group. All primary and secondary outcomes will be compared between the three groups on the basis of the intention-to-treat (ITT) principle. The GEE model can account for intra-correlated repeated measures data and accommodate missing data caused by dropouts, provided the data is missing at random [34], and thus is particularly suitable for ITT analysis, without the need for imputation of missing data.

All data analyses will be performed using the latest version of IBM SPSS (IBM Corp., Armonk, NY, USA). Level of statistical significance will be set at 0.05.

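### Logbook practice at 6 and 9 months is assigned to an available-data GEE with no imputation, so practice among those randomised is likely to be overstated if people leave because they stopped exercising

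*Protocol article*

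**What the plan says.** Section 2.4.2 of the protocol article lists as secondary outcome (d): "Frequency and duration of self-practice of Tai Chi/brisk walking from a self-recorded logbook". Section 2.5 ties the two late visits, at six months (T3) and nine months (T4), to this behaviour: "To monitor the long-term compliance behaviors of subjects on Tai Chi practice and walking exercise, follow-up evaluations will be conducted".

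Section 2.6 sets one rule for all outcomes: "All primary and secondary outcomes will be compared between the three groups on the basis of the intention-to-treat (ITT) principle". The model is a GEE, said to "accommodate missing data caused by dropouts, provided the data is missing at random", and therefore to be usable "without the need for imputation of missing data". No exception is made for practice.

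Sections 2.3.1 and 2.3.2 define adherence in each exercise arm as a compliance rate of at least 80%, and give no denominator for people who leave. The Tai Chi logbook is checked each week at the class, which runs for three months. Walkers are telephoned each week, with no end date given. The sample size section assumes 25% attrition overall, not split by arm or visit.

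**The concern.** For blood pressure, a missing value says little by itself about what the value would have been. For practice it may say a great deal: someone who has given up the exercise has little reason to keep a log or return for a visit. The protocol makes a similar link when section 2.3.1 says that prolonging an intensive programme past 12 weeks leads people to drop out. An available-data model then estimates late practice as if leavers resembled those still logging.

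The stated assumption is also generous on its own terms. Ordinary unweighted GEE generally needs data missing completely at random, or dropout that depends only on covariates in the model. Missing at random is not enough in general.

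What is at stake is the statement about uptake. The Introduction argues that Tai Chi "might well be better taken up and sustained than brisk walking", and the Conclusions name sustainability as part of the overall aim. A result that describes only those still logging does not show how much the people assigned to each exercise went on doing it.

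**Working it through.** **The plan's own figure.** A one-way ANOVA with means 15.5, 9.75 and 4.0 mmHg, SD 20 and 61 per arm gives 81.2% power at the 5% level, consistent with the stated 80%. Then 61 / (1 − 0.25) = 81.3, rounded up to 82 per arm, and 3 × 82 = 246. This point does not affect the sample size; the 25% is used below.

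**Overstatement within an arm.** Let d be the share who have left, m the mean practice of those still logging, and k the practice of leavers as a fraction of m. The mean over all randomised is m × [(1 − d) + d × k], so the available-log mean is too high by the factor 1 / [1 − d × (1 − k)]. With d = 0.25:

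- k = 1 (dropout unrelated to practice): factor 1.00.
- k = 0.25 (for example 30 against 120 min/week, both assumed): 0.75 × 120 + 0.25 × 30 = 97.5, and 120 / 97.5 = 1.23.
- k = 0 (leavers do none): 0.75 × 120 = 90, and 120 / 90 = 1.33.

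For k = 0 the factor is 1.11 at an assumed 10% dropout and 1.67 at an assumed 40%. The same factor applies to the share who are adherent: 60% of those logging is 0.60 × 0.75 = 45% of those randomised.

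**Contrast between arms.** Count leavers as not adherent, so that share of randomised = share of loggers × (1 − d). All arm-specific dropout figures and all shares among loggers are assumptions.

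| Dropout, Tai Chi / walking | Among loggers, Tai Chi v walking | Among all randomised | Difference shown, then over all randomised (points) |
|---|---|---|---|
| 25% / 25% | 70% v 60% | 52.5% v 45% | +10, then +7.5 |
| 20% / 30% | 60% v 70% | 48% v 49% | −10, then −1 |
| 15% / 35% | 60% v 60% | 51% v 39% | 0, then +12 |
| 15% / 35% | 60% v 70% | 51% v 45.5% | −10, then +5.5 |
| 35% / 15% | 70% v 60% | 45.5% v 51% | +10, then −5.5 |

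With equal dropout and leavers at zero, the difference is only multiplied by (1 − d), so it shrinks and cannot change sign.

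**Does the GEE itself correct this?** A large simulation (8,000 per arm, two exercise arms, T2 to T4, all inputs assumed) had 25% of the Tai Chi arm and 40% of the walking arm stop practising by T4. Of those who stopped, 40% and 90% respectively left the study, giving T4 dropout of about 10% and 36%. True mean practice at T4 was 89.6 v 71.3 min/week, a difference of +18.3. The unimputed GEE gave 100.1 v 112.1 (−12.0) with independence working correlation and 100.4 v 112.4 (−12.0) with exchangeable. Keeping earlier visits in the model therefore removed almost none of the bias in this setting. It shows what is possible, not what is expected in this trial.

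**The case against.** A reader might infer that practice at T3 and T4 is taken only from surviving logbooks with dropouts discarded, that adherence is certainly overstated, and that the arm comparison will be distorted. The documents do not support this. Section 2.5 gives the purpose of the late visits and does not say how logbooks are retrieved after month 3. GEE under ITT keeps a leaver's earlier visits; only the later ones are absent. The only attrition figure is one overall 25%, so every unequal-dropout row above is an assumption. These objections stand, and they make the concern conditional.

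It can also be said that the section 2.6 model was never meant for practice. It specifies that "two dummy variables will be set to correspond the three groups with the control as reference" and uses T1 as the time reference, yet the article describes no logbook for controls and none before the intervention starts. That is a fair observation, but the text still places all secondary outcomes under the rule, and the misfit is another reason to give this outcome its own rule. Likewise, the article states no between-arm comparison of the 80% threshold, and its wording on sustainability can be read as sustained risk-factor reduction. The late visits are nonetheless held expressly to follow practice.

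Two further points stand. If logs decline before people leave, methods that use that history could remove some or all of the bias, so it is too strong to say that missing-at-random methods cannot help. And scoring every unlogged week as zero in the main analysis could penalise Tai Chi for losing its weekly log check at month 3 rather than for losing practice.

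**Conclusion.** The concern holds in conditional form. The article fixes an available-data analysis with no imputation for an outcome whose absence is plausibly caused by its own low value. At T3 and T4 the estimate is likely to overstate practice among those randomised, by a factor between 1.00 (dropout unrelated to practice) and 1.33 (leavers do none) at the plan's 25% attrition. This assumes that the full 25% has left by the visit concerned and that leavers practise no more than those who stay.

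It does not follow that the Tai Chi versus walking contrast is wrong. Hiding or reversal needs dropout, or the link between dropout and practice, to differ by arm, and the article gives no figure for either. The primary outcome analysis and the sample size are outside this point. It concerns one secondary outcome, but the one on which any claim of better sustained exercise would rest.

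**What to change.** 1. Exempt outcome (d) from the section 2.6 statement that imputation is not needed.
2. Compare practice, and the 80% compliance rate, between the Tai Chi and walking arms only, with everyone randomised to those arms as the denominator.
3. Report dropout and missing logs by arm and visit.
4. Prespecify an analysis that counts participants as not practising after dropout, and show it beside the available-log GEE. Claim better sustained practice in one arm only if both agree.
5. For participants still in the study, treat unlogged weeks as zero only as a sensitivity analysis, because log checking after month 3 may differ by arm.

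This costs a few lines of analysis text and uses data already collected, with no extra participants or visits. The downside is that the dropout-as-zero analysis understates practice for people who leave but keep exercising; the available-log analysis beside it shows how much the result depends on that.

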### 2.6. Data Analysis

(1)For demographic data, frequency and percentage will be used to summarize and present categorical variables, whereas mean and SD will be used for continuous variables. Normality of continuous variables will be examined using skewness and kurtosis statistics and normal probability plot. The baseline characteristics among the three groups will be compared using chi-square test and one-way analysis of variance (ANOVA).(2)Generalized estimating equations (GEE) models with appropriate link function and distribution assumption, will be used to compare the changes in outcome variables across time among the three groups with adjustment for those baseline characteristics showing statistically significant differences among the groups. In the GEE model for each outcome, two dummy variables will be set to correspond the three groups with the control as reference. Another three dummy variables will be set to represent the four time points (T1 to T4) with the baseline (T1) as the reference. The interaction-terms of group by time will also be included in the GEE models to assess the differential changes of the outcomes across time and between group. All primary and secondary outcomes will be compared between the three groups on the basis of the intention-to-treat (ITT) principle. The GEE model can account for intra-correlated repeated measures data and accommodate missing data caused by dropouts, provided the data is missing at random [34], and thus is particularly suitable for ITT analysis, without the need for imputation of missing data.

All data analyses will be performed using the latest version of IBM SPSS (IBM Corp., Armonk, NY, USA). Level of statistical significance will be set at 0.05.

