#### Sample Size and Randomization

A previous study conducted in the Asia-Pacific region reported that SBP is an important marker of risk of CVD in people with and without diabetes. A given reduction in SBP is likely to have similar relative effect on reducing the risk of a cardiovascular event, regardless of diabetes status [21]. SBP is therefore being set as the primary outcome and for sample size calculation.

A previous local study on a Tai Chi program reported a mean reduction of 15.6 mmHg (standard deviation, SD = 7.9) in the intervention group and a mean increase of 6.4 mmHg (SD = 10.5) in the control group [22]. Another pre-post study showed a mean reduction of 8.7 mmHg (SD = 15.6) in SBP after receiving a walking program in obese postmenopausal women [23]. We based our sample size calculation conservatively on discriminating among a mean SBP reduction of 15.5 mmHg in the Tai Chi group, 4.0 mmHg in the control group, and 9.75 mmHg (the grand mean) in the walking group. Further conservatively assuming an SD of 20.0, G*Power gives that 61 subjects per arm will be needed to achieve a power of 80% at a significance level of 5%. To further take into account a potential attrition rate of 25% [12], 246 subjects (82/arm) will be targeted.

A computer-based randomizer will be used for random allocation of subjects [24]. Eligible subjects will be randomly assigned to the three groups in 1:1:1 ratio according to their sequence of enrolment into the study and the corresponding sequentially listed group identifiers generated by the randomizer in advance. The random group identifiers list will be stored in a password-protected computer and only be accessible by the staff who are responsible for group allocation.

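### Choosing GEE covariates by baseline significance tests selects chance differences, forgoes available precision, and leaves baseline blood pressure imbalance in the change contrast

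*Protocol article*

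**What the plan says.** All of this is in the protocol article. Under Sample Size and Randomization, allocation follows a computer-generated list: "Eligible subjects will be randomly assigned to the three groups in 1:1:1 ratio".

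Section 2.6 (Data Analysis) then has two linked steps. First: "The baseline characteristics among the three groups will be compared using chi-square test and one-way analysis of variance (ANOVA"). Second, the GEE models for the outcomes are fitted "with adjustment for those baseline characteristics showing statistically significant differences among the groups". The only level given is general: "Level of statistical significance will be set at 0.05". No covariate is named in advance and no prognostic reason for choosing one is given.

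The same section fixes the rest of the model: two group dummies (control as reference), three time dummies for four visits (T1 as reference), and "The interaction-terms of group by time will also be included in the GEE models". T1 is therefore part of the outcome vector, and the treatment effect is read as a difference in change from T1. Missing data are left to the GEE without imputation, on the condition that they are missing at random.

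**The concern.** After randomisation, a significant baseline difference shows only that chance produced an imbalance. It does not show that the variable predicts blood pressure, its change, or dropout. A rule based on it can admit irrelevant variables and pass over important ones, and nobody can write down the final model before the baseline data are tested.

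Three things are at stake for the SBP result: precision that baseline data could supply, protection against chance imbalance in baseline SBP, and the credibility of the missing-at-random condition, which depends on what the model conditions on. This is a method that the protocol fixes, not a detail left to a later analysis plan.

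**Working it through.** **Inputs from the article.** Randomised 1:1:1; significance level 0.05; 82 per arm recruited and 61 per arm expected to be analysed; "a mean SBP reduction of 15.5 mmHg in the Tai Chi group, 4.0 mmHg in the control group, and 9.75 mmHg" in the walking group; "Further conservatively assuming an SD of 20.0".

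**Assumptions, because the article gives no figure.** Number of baseline characteristics tested, k = 5 to 20, independent. Correlation between SBP visits, ρ = 0.5 or 0.7. SD of SBP level 20 mmHg. (The article's SD of 20 is attached to reductions. With equal variances the SD of change is the SD of level × √(2(1−ρ)), so the two coincide at ρ = 0.5.)

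**1. The plan's own figure.** A three-group F test with means 15.5, 9.75 and 4.0 and SD 20 has f = 0.2347. Power is 80.5% with 60 per arm and 81.2% with 61, so "61 subjects per arm will be needed to achieve a power of 80% at a significance level of 5" per cent is reproduced to within one patient. 61/0.75 = 81.3, hence 82 per arm and 246 in total. The covariate rule does not affect these figures.

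**2. How often chance selects something.** P(at least one) = 1 − 0.95^k: 22.6% (k = 5), 40.1% (10), 53.7% (15), 64.2% (20).

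**3. How large an imbalance escapes.** With the third arm midway, F = n·d²/4, where d is the standardised difference between the outer arms. At the 5% critical value, d = 0.38 with 82 per arm (0.45 with 61). This corresponds to a pairwise z of √(2 × 3.05) = 2.47, which is a ceiling.

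**4. What a selected covariate does in this GEE.** One simulated data set, 82 per arm, exchangeable correlation, group by time, with and without a time-fixed prognostic covariate as a main effect:
- Complete data: the interaction estimates were −5.862 and −11.893 both ways, with identical standard errors.
- 25% of follow-up visits missing at random: −4.246 against −4.196, and −9.751 against −9.657.

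A covariate that shifts every visit equally cancels from a change contrast.

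**5. Baseline SBP imbalance.** A baseline difference D between two arms carries into the change contrast as (1−ρ)·D through regression to the mean. At z = 1.9, which the three-group test need not flag, D = 1.9 × 20 × √(2/82) = 5.9 mmHg.
- ρ = 0.5: 0.5 × 5.9 = 3.0 mmHg.
- ρ = 0.7: 0.3 × 5.9 = 1.8 mmHg.

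The planned step between adjacent arms is 15.5 − 9.75 = 5.75 mmHg.

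If baseline SBP is flagged and enters as a main effect while T1 is also an outcome, nothing is repaired. In a simulated data set (ρ = 0.5, complete data) the T2 interaction was 2.840 (SE 3.005) with and without it. Only the group main effect and the working correlation moved (the latter from 0.47 to 0.18). When baseline was allowed to act on the follow-up values, the estimate became 4.253 (SE 2.556).

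**6. Precision given up.** With equal variances, the variance with baseline as covariate divided by the variance of the change contrast is (1−ρ²)/(2(1−ρ)) = (1+ρ)/2: 0.75 at ρ = 0.5 and 0.85 at ρ = 0.7. The change contrast has SE √(2 × 2 × 400 × 0.5/82) = 3.12 mmHg at ρ = 0.5. Baseline as covariate gives 3.12 × √0.75 = 2.70. A simulated data set gave 3.12 and 2.60.

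**7. Dropout.** In an illustration with dropout assumed to depend on arm and on a covariate, including that covariate cut the bias from about −1.7 to −0.4 mmHg. The size depends wholly on the assumed mechanism.

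**8. Overall type I error.** In a simulation of a single follow-up comparison (6,000 runs per setting, 61 per arm), the significance-selected analysis rejected a true null in 4.7%, 4.5% and 3.8% of runs for covariate-outcome correlations 0.3, 0.5 and 0.7.

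**The case against.** The strongest reply is that the rule is nearly inert here. The effect is read from group by time with T1 in the outcome vector, so a time-fixed main effect cancels whether it is chosen well or badly. That is correct with complete data, and with visits missing at random the shift in step 4 was about 0.1 mmHg or less. A chance-selected irrelevant covariate therefore does little damage, and the 40% is a count of unhelpful selections, not a measure of bias.

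A reader might infer that the test itself is compromised. For a covariate correlated 0.3 to 0.5 with the outcome, P(|N(rz, √(1−r²))| > 1.96) gives a conditional type I error of 8% to 12% at z = 1.9 and 10% to 20% at z = 2.47. The arithmetic is right, but it describes an unadjusted comparison of follow-up levels, or a covariate with that correlation with change. The article plans neither a level comparison nor gives any such correlation. In a simulation of the change contrast, with covariates correlated 0.3 to 0.5 with SBP at every visit, the conditional rate was 4.8% to 5.5%.

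It may also be said that the rule is stated in advance, mechanical, and uses baseline data only. That stands: it gives no opening to select on outcome results. Nor does section 2.6 say outright that baseline SBP is among the characteristics tested, since its first item opens with demographic data. If it is not, the rule never addresses baseline SBP; if it is, step 5 shows that the adjustment does not work.

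What the reply does not answer is that a rule with no useful effect when triggered is the only covariate adjustment the article provides.

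**Conclusion.** The point holds in a limited form. The rule selects chance differences, ignores prognostic strength and any link with dropout, and leaves the covariate set open until baseline data are tested. It does not inflate overall type I error, and the documents do not support a claim of a conditional false-positive rate of 8% to 20% in the planned model.

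The cost is forgone benefit. Using baseline as a covariate would cut the variance of the SBP contrast by 25% at ρ = 0.5 or 15% at ρ = 0.7. The plan as written leaves an imbalance at z = 1.9 contributing about 3.0 or 1.8 mmHg to the change contrast. That bias is conditional on the imbalance observed and averages out over randomisations. These sizes rest on the assumed visit correlations, equal variances and a level SD of 20 mmHg. The 40% rests on 10 independent variables, and the dropout figure is an illustration only. The point should be corrected, but it does not threaten the validity of the trial or its sample size.

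**What to change.** In section 2.6, delete the significance-based adjustment and the baseline hypothesis tests, and keep a descriptive baseline table by arm. In their place, prespecify for every outcome, whatever imbalance is observed:

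- the baseline value of that outcome as a covariate, with T2, T3 and T4 as the outcomes and group contrasts read at each visit;
- a short fixed list chosen on prognostic grounds from data already collected, for example age, sex, antihypertensive medication at baseline and recruiting clinic, entered so that they can act on the follow-up values. Adding them as main effects to the present model with T1 as an outcome would change almost nothing.

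The cost is one or two sentences, recoding of the time dummies and a few degrees of freedom. No new data and no change in sample size are needed. Participants with no follow-up value would not enter this model, so their number should be reported by arm.
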